## Abstract

**Background:**

Non-pharmacological approaches for the management of migraine exhibit low to moderate effectiveness due to a lack of high-quality randomized clinical trials. In fact, previous studies applied isolated techniques, which were not representative of common clinical practice. A multimodal approach for migraine may benefit these patients more than isolated approaches. This randomized clinical trial aims to determine the effectiveness of a multimodal protocol combining manual therapy, exercise, and therapeutic pain neuroscience education versus the application of manual therapy or pain neuroscience education alone in patients with migraine.

**Methods:**

This clinical trial will include 75 individuals of both sexes, aged between 18 and 55 years, with migraine. Participants will be randomized into three groups: the therapeutic pain neuroscience education (TPNE; *n* = 25) group, the manual therapy (MT; *n* = 25) group, and the multimodal (MM; *n* = 25) group. The TPNE group will receive one orientation session on migraine and pain self-management, and recommendations for daily active stretching and walking, with subsequent therapist monitoring. The MT group will receive manual therapies targeting musculoskeletal disorders of the cervical spine. The MM group will receive manual therapies targeting musculoskeletal disorders of the cervical spine, active neck exercises, and therapeutic pain neuroscience education. The treatment period will last 12 weeks. The primary outcome will be the headache impact, measured using the Headache Impact Test (HIT-6). Secondary outcomes will include migraine frequency and intensity, cervical mobility and strength parameters, neck pain-related disability, kinesiophobia, cutaneous allodynia, pain-related catastrophizing, quality of life, and self-perception of change. All outcomes will be evaluated at the fourth, eighth, and twelfth weeks of the treatment period. Primary and secondary clinical outcomes, such as headache impact, frequency, and intensity, will also be evaluated at the 1-, 2-, and 4-month follow-ups.

**Discussion:**

The results of this randomized clinical trial may provide high-quality clinical evidence of the effects of non-pharmacological treatment options for the management of migraine.

**Trial registration:**

This study was registered under the access code RBR-7s22c75 in the *Registro Brasileiro de Ensaios Clínicos* (ReBEC) in December 2020.

## Background

Migraine, a neurological disease, is considered the second leading cause of disability, affecting one billion people worldwide [1]. This disease is characterized by attacks of unilateral, recurrent, pulsating headache of moderate to severe intensity that lasts for 4–72 h and increases with daily routine or physical activity, and may be accompanied by nausea and/or photophobia and phonophobia [2]. Currently, pharmacological treatment has the highest level of evidence for managing migraine [3]. However, non-pharmacological approaches [4, 5], for e.g., acupuncture, self-management techniques, pain neuroscience education, relaxation strategies, mindfulness, and physical therapy [5–7], are also extensively used by patients.

Physiotherapy, a conservative, non-invasive, non-pharmacological intervention, is used as an adjuvant to pharmacological treatment of headache, and presents evidence of decreasing the frequency and intensity of migraine attacks [8–11]. Manual therapy with trigger point release, spinal mobilization/manipulation, and cervical stretching, present similar evidence to pharmacological therapy for reducing the frequency and intensity of headache [9, 10, 12, 13]. Moreover, there is also moderate- to low-level evidence for electrotherapy [14] and aerobic exercises [11, 15] for migraine. However, these techniques have been tested only separately, without associating them with different headache management approaches.

Therapeutic pain neuroscience education has also been shown to be an evidence-based clinical approach that provides additional benefits, when associated with pharmacological therapy, for reducing headache frequency [16–18]. Kindelan-Calvo et al. [19] found strong evidence supporting an improvement in disability and a decrease in the frequency of headaches after the application of therapeutic pain neuroscience education in migraineurs.

Craniocervical exercises may also be beneficial for patients with migraine, as they have proven to be effective in individuals with neck pain and other headaches associated with cervical spine impairments [20–22]. However, no systematic review has determined its effectiveness in this population. Considering the decrease in cervical muscular performance [23, 24] and cervical muscle resistance [25] in women with migraine, these patients could also benefit from associated exercise programs. It has already been proven that different musculoskeletal and functional dysfunctions accompany migraine headaches. Furthermore, it has been suggested that patients with migraine could benefit from multimodal treatment that includes relaxation techniques, manual therapy, stretching, and active neck exercises, in addition to therapeutic pain neuroscience education. No study has investigated the additional effects of these interventions in a population with migraine.

The primary aim of this randomized clinical trial will be to determine the effectiveness of a multimodal approach combining manual therapy, exercises, and therapeutic neuroscience pain education on the severity of headache in individuals with migraine. The secondary aims will be to determine its effectiveness on headache frequency (days/month), intensity, pressure pain sensitivity, cervical mobility, and related functions. We will also analyze if there were effects on neck pain-related disability, cutaneous allodynia, kinesiophobia, pain-related catastrophizing, global self-perception of change, and the patient’s quality of life. Thus, we hypothesize that the multimodal physical therapy protocol, which associates multiple interventions with patient education, will help reduce migraine disability, when compared to the application of each intervention alone.

## Methods

### Design

A three-armed, parallel-group, randomized clinical trial with a 12-week treatment protocol and follow-up assessments after 1, 2, and 4 months will be conducted according to CONSORT guidelines [26]. This treatment protocol will be described in accordance with the SPIRIT recommendations [27].

### Setting

The study will adhere to the guidelines provided by the International Headache Society (IHS) for clinical trials, with respect to the inclusion and exclusion criteria, outcome measures, and statistical analysis. The study protocol has been approved by the local ethics committee (CAAE 36575220.5.0000.5440), and the trial was registered under the access code RBR-7s22c75 in the *Registro Brasileiro de Ensaios Clínicos* (ReBEC) in December 2020. All participants will receive and sign an informed consent form before the beginning of the trial.

The evaluations and interventions will be conducted at the *Hospital das Clínicas* of the Ribeirão Preto Medical School of the University of São Paulo (HCFMRP-USP) and the Laboratory of Evaluation of Posture and Human Movement of the Ribeirão Preto Medical School. The study will include three primary researchers; two will be responsible for data collection, and the third one will be responsible for treatments.

### Participants

Inclusion criteria are individuals of both sexes, aged between 18 and 55 years, and diagnosed with migraine according to the 3rd edition of the IHS (ICHD-III), with at least three days of migraine per month in the previous month.

Exclusion criteria will include other concomitant primary/secondary headaches, history of facial or neck trauma, history of cervical disc herniation or cervical osteoarthritis, any systemic degenerative disease (e.g., rheumatoid arthritis, lupus erythematosus), pregnancy, physiotherapeutic treatment of the craniocervical region in the previous year, and/or having started a new pharmacological treatment for migraine in the 3 months prior to participating in the trial.

### Interventions

#### Therapeutic pain neuroscience education (TPNE)

Twenty-five participants will be randomly assigned to this group, which will be the active control group. They will attend a single appointment of approximately 60 min aimed at addressing pain neuroscience education, adapted from the protocol by Holroyd et al. [16] and complemented with materials from the Pain Research group (Brazil) [28] for neuroscience-based pain education. The therapist, with 4 years of clinical experience in this approach, will instruct the subjects on the pathophysiology of migraine, identification of prodromal warning signs and possible triggers, management of disease-related behavioral skills, and training relaxation techniques (stretching, deep breathing, progressive muscle relaxation, and relaxation images) in a single session, of approximately 50 min [16]. In addition, the participants will receive educational material containing home-based recommendations for daily activities during the 12 weeks of treatment, including those on self-management of migraine attacks, self-massage, active stretching, and the practice of physical activities, such as walking for 30–40 min. Patients reporting vestibular symptoms and/or a history of falls will also be instructed to perform basic home exercises to control balance, with both eye and head movements [29]. After this session, participants will be contacted weekly by the therapist through phone calls or mobile messages to assess their orientations adherence and solve any questions or problems regarding the exercises.

#### Manual therapy (MT)

Twenty-five participants will be randomly assigned to this group and will receive treatment once a week, for 12 weeks, with each session lasting approximately 40 min, from a physical therapist with 4 years of clinical experience. The protocol of this group was based on the protocol by Bevilaqua-Grossi et al. [9], with no home-based orientations.

It consist of the following five steps: 1, Diaphragmatic respiratory training for 5 min guided by the therapist [9, 30], combining a profound inhalation using the diaphragm and a gentle exhalation which ends up with a conscious contraction of abdominal muscles; 2, cervical spine traction mobilization for another 5 min, with slow, progressive, and intermittent traction of the occiput timed with the diaphragmatic breathing [31]; 3, deep massage and myofascial release of craniocervical muscles for 15 min, especially the suboccipital, upper trapezius, sternocleidomastoid, and scalene muscles; 4, 10 min to trigger points ischemic compression, applying a 90 s compression at a maximum of six trigger points identified in the craniocervical muscles according to the most recent criteria [32]. The points to be treated will be chosen according to the intensity of pain at that point (0–10) and reproduction of headache symptoms. The session will end up at the fifth step, which consist of three repetitions in each direction of passive stretching of neck muscles (flexion, lateral flexion, and rotation associated with ipsilateral flexion) sustained by 30 s.

#### Multimodal group

The participants randomly allocated to the multimodal group will receive treatment from a physical therapist with 4 years of clinical experience, once a week, for 12 weeks, with each session lasting approximately 50 min. The proposed protocol is based on the available evidence using isolated treatments for the management of the most prevalent musculoskeletal disorders observed in patients with migraine [9, 33]. Treatment will consist of combined techniques for relaxation, stretching, and myofascial release, focusing primarily on craniocervical muscles, with an exercise program for the cervical muscles as proposed by Falla et al. [33], as well as therapeutic pain neuroscience education. Participants will be instructed to practice cervical exercises once a day during the treatment period, with weekly reminders sent via SMS, WhatsApp®, or e-mail to perform these exercises.

The first treatment session will cover the same therapeutic pain neuroscience education program as the TPNE group [16, 28]. During treatment, time will be reserved during the session to reinforce and continue the pain education. The participants will receive in the initial session an educational material containing home-based recommendations for daily activities during the 12 weeks of treatment.

The participants will receive educational material containing home-based recommendations for daily activities during the 12 weeks of treatment, including those on self-management of migraine attacks, self-massage, active stretching, and the practice of physical activities, such as walking for 30–40 min.

From the second session, the protocol will follow the same interventions mentioned in the MT, changing only the time of massage/myofascial release to five min, adding 15 min to the active flexor and extensor muscle exercises [33], and 5 final minute of general orientation [16, 19]. The exercise program will consist of two stages, adapted from the protocol described by Falla et al. [33]. The first stage will last 8 weeks, consisting of flexion and extension exercises of the cervical spine. The incremental craniocervical flexion will be performed in a relaxed supine position, without a pillow, in two sets of 10 repetitions with 10 s of support. For craniocervical extension, participants will perform craniocervical extension, flexion, and rotation in a supine position with elbows supported, keeping the cervical spine neutral. Two sets of 10 repetitions will be carried out, which can progress to up to three sets of 10 repetitions. The series, repetitions, or time of support in the posture will increase according to the patient’s tolerance. There will be an adjustment of the schedule if the participant is unable to perform it. The second stage will be 4 weeks in duration and will feature high-load exercises, both for flexion and extension, with the head weight as the load. Head flexion will be preceded by cervical flexion in the supine position, in three series of the 15 repetitions, and maintained until the end of the protocol. For the neck extension exercise, the patients will be instructed to keep the craniocervical region in the middle position while extending the cervical region, which will be performed in 4-pt kneeling. This will also be done in three series of the 15 repetitions until completion of the protocol.

The general orientation time will be dedicated to complementing the patient’s therapeutic pain neuroscience education, reinforcing the orientation and management approach of the first session, and to solve the possible existing doubts of the participants.

Individuals from all intervention’s groups will be advised not to start any new treatment and not change their current medication use during the trial. There will be no possibility to change allocated interventions and treatments will be discontinued only if the participant request.

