### Sample size

The sample size was calculated for the primary outcome, the HIT-6. It was based on a mean reduction of six points and a standard deviation of 6.03, while adopting a significance level (α) of 0.05 and power of 90%. We estimated 21 individuals per group, and considering a 15% loss to follow-up, 25 individuals per group will be required. Therefore, 75 individuals will be included in this clinical trial. An effect size of ≥ 6 points at HIT-6 is the minimum clinically important difference (MCID) for this scale [34]. The standard deviation was derived from a sample of nine volunteers from our database of previous studies.

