### Statistical methods

A descriptive analysis of all variables will be performed, and the data will be reported as mean, standard deviation, and 95% confidence intervals. The statistical analysis will be performed according to the nature and distribution of each variable and be evaluated to verify any changes in the parameters and differences between the groups after the end of the protocol. For the analysis of outcomes, a significance level of 0.05 will be considered.

The intention-to-treat analysis will include all randomized volunteers, regardless of their treatment adherence in the evaluations and analyses [56]. The between-groups comparison will be performed using a mixed-effect regression model for all outcomes, considering the group effect, time effect, and group vs. time interaction. In addition, in those outcomes without predetermined MCID values, it will be calculated based on a distribution-based approach. The clinical relevance of the differences between groups will be classified according to the combination of MCID and effect size (ES), as suggested by Armijo-Olivo et al. [57]. The ES will be estimated by using Cohen’s d. The clinically relevant difference should present a mean difference that is more significant than MCID and ES > 0.4.

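### The discontinuation rule allows treatment to stop only at the participant's request, so as written no clinician can stop the hands-on neck treatment for safety

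*Protocol article*

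**What the plan says.** The rule closes the Multimodal group section, in a paragraph that opens by addressing participants in every group: "There will be no possibility to change allocated interventions and treatments will be discontinued only if the participant request". It therefore governs all three arms.

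The treatment it governs is described under Manual therapy (MT). That arm has weekly sessions for 12 weeks that include "cervical spine traction mobilization for another 5 min, with slow, progressive, and intermittent traction of the occiput", deep massage, 90-second ischemic compressions "at a maximum of six trigger points identified in the craniocervical muscles", and sustained passive neck stretching. For the MM arm, session 1 covers the education program, and then "From the second session, the protocol will follow the same interventions mentioned in the MT", with shorter massage and added neck exercises. On those exercises the article says: "There will be an adjustment of the schedule if the participant is unable to perform it".

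Under Participants, the entry exclusions include "history of facial or neck trauma, history of cervical disc herniation or cervical osteoarthritis". Under Statistical methods, the intention-to-treat analysis keeps every randomized person "regardless of their treatment adherence in the evaluations and analyses".

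**The concern.** An article may leave adverse-event handling to the full protocol, and silence on it would not be a finding. This sentence is not silent. It names one ground for stopping and excludes all others. If the full protocol contains a safety stop, the article misstates it. If it does not, the gap is real.

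Patient safety is what is at stake. The protocol itself treats neck trauma and cervical disc herniation as reasons not to enter the trial. If one of them arises in week 5, the rule as written gives the therapist no ground to end treatment, although the therapist may be the first to see the problem. A sensible stop would then be a departure from the protocol.

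**Working it through.** **1. Does any other text permit a clinician-initiated stop?**

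| Provision | Section | What it does | Is it a stop? |
|---|---|---|---|
| Tolerance-based progression and schedule adjustment | Multimodal group | Adapts the MM exercise program only; MT has no equivalent | No |
| Choice of trigger points by pain and headache reproduction, at most six | Manual therapy (MT), carried into MM | Sets the dose in a session | No |
| Exclusions for neck trauma, disc herniation and others | Participants | Applied at entry | No |
| Unblinded therapist, medication use | Limitations | Discusses bias and co-intervention | No |

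None of these gives the therapist or investigator authority to end treatment.

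**2. Planned exposure under the rule.** Inputs are 25 participants per arm and weekly sessions for 12 weeks, with hands-on treatment in MM from session 2.

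- MT: 25 × 12 = 300
- MM: 25 × (12 − 1) = 275
- Total: 575 sessions in 50 participants, at full attendance

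**3. Would adding a safety stop damage the trial?** The plan's own figure comes first. The Sample size section uses a difference of 6 points, SD 6.03, alpha 0.05 and power 90%, and concludes: "We estimated 21 individuals per group, and considering a 15% loss to follow-up, 25 individuals per group will be required". The normal approximation gives n = 2 × [(1.960 + 1.282) × 6.03 / 6]² = 21.2 per arm, or 22 rounded up, against 21 stated. Power at 21 per arm is 89.7% by the normal approximation and 88.2% by the t-test. Inflation gives 21 / 0.85 = 24.7, so 25. The plan's figure reproduces to within one participant per arm.

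Now suppose k participants in the MM arm are stopped and each loses the entire 6-point benefit. Both k and the full loss are assumptions. The MM-versus-comparator difference becomes 6 × (n − k) / n. Power is for one pairwise two-sided t-test with SD 6.03.

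| k | Difference, n = 25 | Power, n = 25 | Difference, n = 21 | Power, n = 21 |
|---|---|---|---|---|
| 0 | 6.00 | 93% | 6.00 | 88% |
| 1 | 5.76 | 91% | 5.71 | 85% |
| 2 | 5.52 | 89% | 5.43 | 81% |
| 3 | 5.28 | 86% | 5.14 | 77% |

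Mixing full responders with complete non-responders also widens the MM variance, by 36 × (k/n)(1 − k/n).

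- n = 25, k = 3: 36 × 0.12 × 0.88 = 3.80. The pooled SD is √(6.03² + 3.80/2) = 6.19 and power is 84.1%.
- n = 21, k = 3: 36 × 0.143 × 0.857 = 4.41. The pooled SD is √(6.03² + 4.41/2) = 6.21 and power is 74.5%.

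**The case against.** The strongest reply is that the finding rests on one word in a condensed article. The surrounding text concerns treatment fidelity: no new treatments, no medication changes, no crossover. Read that way, the sentence says only that investigators will not remove people for poor adherence or response, which fits the intention-to-treat statement. Ethics approval was obtained, and a full protocol may well contain a safety stop. The techniques are mild (slow intermittent traction, massage, stretching, no thrust manipulation listed), and they are given by a physical therapist with 4 years of experience. A rule about ending treatment also need not force a therapist to deliver a given component to an injured person.

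Much of this stands. The benign intent is plausible, the described risk looks modest, and nothing here shows that the trial lacks a safety stop in practice. It does not rescue the sentence, which states an exclusive rule and makes no exception for safety. Clinical discretion within a session is not authority to end the course.

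A second point also stands: the remedy hands a judgement to a therapist who, as the Limitations section says, cannot be blinded, in a trial whose primary outcome is self-reported. That is why the threshold has to be written down. Finally, the power figures are peripheral. They assume that someone with a contraindication would have gained the full 6 points by continuing, so they bound the cost of the fix and say nothing about the fault.

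**Conclusion.** The concern holds. As written, the rule bars a clinician-initiated safety stop in every arm, and this matters most in MT and MM, where 575 hands-on neck sessions are planned in 50 participants. The conclusion rests on the literal reading of the sentence and on the article alone. It claims no probability of harm, because the article gives no adverse-event rate, and no effect of the current wording on the primary estimate. It is a cheap safety improvement that should be made; it does not threaten the validity of the trial.

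**What to change.** Replace the second half of the sentence with wording such as:

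> Allocated treatment stops when the participant asks. The therapist or investigator may also stop it for a serious or treatment-related adverse event that makes continuing unsafe, or for a new contraindication to the allocated treatment (for example, neck trauma or cervical disc herniation arising during treatment). Transient soreness, poor adherence and poor response are not grounds for stopping. The reason is recorded, and the participant stays in all scheduled evaluations and in the intention-to-treat analysis.

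The named non-grounds preserve the likely intent of the present rule and limit discretion by an unblinded therapist. Retention in the analysis applies what Statistical methods already provides.

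The cost is one sentence, one recorded field and an ethics notification. The sample size stays at 25 per arm. The downside is possibly a few more treatment stops. Under the worst-case assumptions above, three stops in MM would take pairwise power to about 84–86% with 25 evaluated per arm, or 74–77% with 21; the lower figure in each range allows for the wider variance. If nobody needs such a stop, power is unchanged.
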